
### Intervention impact measures

Data from the following measures will be collected at the baseline and follow-up to support the feasibility objectives. Provided they are deemed feasible and acceptable, they will be considered for inclusion in a future definitive trial.

#### Primary outcome

The primary outcome was reference child BMI z-score (age- and gender-adjusted height(m)/weight(kg)^2^) measured by NatCen interviewers.

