### Feasibility outcomes

The feasibility outcomes were as follows:Recruitment rate, including number of local authorities screened for eligibility, reason for ineligibility and number (and reason) for declining; number agreeing to take part (including number of nominated centres); number of centres agreeing to take part (and reason for those declining); number of parents approached; number (and proportion) agreeing to researcher contact; number (and proportion) of eligible parents consenting; number of parents self-referring; and reasons for parent ineligibility and non-consent.Training and quality assurance, including length of time taken to train and certify staff to deliver HENRY programme; number of staff attending training; number of staff certified to delivery HENRY; changes in knowledge and practice before and after training (from pre and post training facilitator questionnaire); and programme delivery quality assurance (collected routinely by HENRY).Contamination identification and risk, ascertained through determining the number of parents registered to control centres attending centres running HENRY; HENRY-trained facilitators working in or visiting control centres and proportion of their time spent working in other centres; control and intervention centres merging with other centres; other schemes addressing lifestyle change attended by parents during the study; parents registered to control centres who have had contact with parents attending centres running HENRY. We will also assess the frequency of contact between parents in HENRY and control centres. Risk will be estimated by triangulating identified sources of contamination with outcome data and qualitative assessment of perceived contamination.Acceptability of data collection protocol, assessed from the number, proportion and timing of parent withdrawals from HENRY programme (intervention centres only) and follow-up data collection (both parents registered to HENRY and control centres) out of those registered and reasons for withdrawal; number (and proportion) of registered parents lost to follow-up; number (and proportion) of parents with self-reported questionnaire and height/weight data; and missing item level data on questionnaires. Feedback will be gathered from parents, centre staff and commissioning leads via interviews and focus groups.Determination of sample size for definitive trial estimated using feasibility data: variability of gender-adjusted body mass index (BMI) in both arms; difference between arms and 95% confidence intervals; and estimation of clustering effect (ICC) and cluster size.Intervention compliance and implementation, estimated from routinely gathered data on timing of delivery of first HENRY programme (plus reasons if delivery occurs later than 4 weeks after training); number of HENRY courses delivered per centre; and attendance rates at HENRY programmes and reasons for absence.

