#### Secondary outcomes

Secondary outcomes were as follows:Primary caregiver BMI (measured height(m)/weight(kg)^2^) and waist circumference (cm).Family eating/activities using the validated Golan Family Eating and Activity Habits Questionnaire (21 items) [24] assessing activities such as leisure time activities, eating habits and style, hunger and satiety cues, exposure to and availability of problematic foods and stimulus control, and frequency of parent and child eating meals and snacks together.Parenting self-efficacy, gathered via the Dumka Parenting Self Agency Measure (5 items) [25]. This questionnaire measures parents’ overall confidence in their ability to act successfully in their parental role.Feeding, collected via the Baughcum pre-schooler feeding questionnaire (37 items) [26]), used to measure maternal feeding practices, child eating behaviours and maternal beliefs.Dental health via a bespoke questionnaire based on the Dental Health Survey of Children and Young People by the University of Leeds, School of Dentistry, to measure the potential wider impact of HENRY and a child’s dental health (Dental Questionnaire). This contains 6 questions related to tooth brushing and dental attendance and whether the child has received general anaesthetic treatment.

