### Statistical analysis

Recommendations for feasibility studies suggest that at least 30 participants per group will allow sufficient precision when estimating study summary measures [34]. We plan to recruit two local authorities and 120 parents to give confidence that a phase III multi-centre trial can be successfully conducted [34, 35].

As this is a feasibility study, the analysis will focus on descriptive statistics and confidence interval (CI) estimation rather than formal hypothesis testing (i.e. no formal evaluation of the study interventions will be conducted as part of this feasibility study). The trial is not powered to provide a precise estimate of the level of clustering relating to group effects, but it will allow an investigation of this effect, which will inform the sample size estimation for the definitive trial. No formal analyses are planned until after the trial is closed to recruitment and follow-up and the required number of local authorities/centres have been randomised and the required number of parents have been registered. Final analysis will be carried out when all available outcome data has been collected.

The feasibility and success of the recruitment strategy will be evaluated by summarising the screening, eligibility, consent and randomisation/registration processes, including the numbers of local authorities/centres/parents involved during each stage. Reasons for non-participation in the study will be summarised. The total number of parents registered will be summarised, overall, by month/programme (as appropriate) by centre and local authority. The length of time taken to train and certify staff to deliver the HENRY programme will be detailed by HENRY staff. The number of staff attending training/certified will be summarised overall and by centre. Facilitator response to training will be captured as part of the process evaluation.

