Participant retention during follow-up, including the number of centres/parents withdrawing from the study and the timing of and reasons for the withdrawal will be presented overall, by arm and time-point. We will also report losses to follow-up over time. We will also report the difference and its confidence intervals (CI) for follow-up rates between the intervention and control groups (to identify large differences between the arms). Levels of missing self-reported outcome data, both at the individual item level and for entire outcome measures will be reported overall, by time-point and by treatment arm.

Centre environment, family eating/activities, parenting self-agency, pre-schooler feeding and dental health at baseline and at 12 months post registration will be summarised overall, by arm and by time-point and where appropriate by centre (centre environment). 95% CI will be constructed for the differences in these outcomes between control and intervention groups. Mean activity per day will be summarised overall, by arm and by time-point.

In order to inform the sample size calculation for the definitive trial, we will calculate the gender-adjusted BMI, overall and per arm together with corresponding 95% CI. We will also compare the variability of gender-adjusted BMI between arms. As variation surrounding the intra-class correlation coefficient (ICC) estimate is likely to be large, we will estimate the ICC after controlling for covariates and constructing a CI [34, 36] to obtain a range of plausible estimates from which a variety of sample sizes can be calculated. A conservative approach would be to use the 80% upper one-sided confidence limit of the ICC estimate [34] in the sample size calculations.

To assess compliance with and fidelity of delivery of HENRY, the timing of delivery of the first HENRY programme will be summarised overall and by centre. Reasons for delivery post 4 weeks after receiving training will be presented by centre. In addition, the number of HENRY programmes delivered per centre, attendance rates and reasons for absence will be presented.

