## Abbreviations

BMI: Body mass index (height(m)/weight(kg)^2^)
CTRU: Clinical Trials Research Unit
HENRY: Health Exercise Nutrition for the Really Young
ICC: Intra-class correlation coefficient
NatCen: National Centre for Social Research
TSC: Trial Steering Committee

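### The BMI formula is printed inverted (height over weight squared) in the primary outcome, the caregiver secondary outcome and the abbreviations, although the outcomes are correctly named

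*Protocol article*

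**What the plan says.** The protocol article gives a formula for BMI in three places.

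- *Primary outcome*: "reference child BMI z-score (age- and gender-adjusted height(m)/weight(kg)^2^) measured by NatCen interviewers".
- *Secondary outcomes*: "Primary caregiver BMI (measured height(m)/weight(kg)^2^) and waist circumference (cm".
- *Abbreviations*: "BMI: Body mass index (height(m)/weight(kg)^2".

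Two other places use BMI without a formula. *Feasibility outcomes* lists "variability of gender-adjusted body mass index (BMI) in both arms", with the arm difference and the ICC, as material for sizing the definitive trial. *Statistical analysis* states that "we will calculate the gender-adjusted BMI, overall and per arm together with corresponding 95% CI", also to inform that sample size. The correct expression is not printed anywhere in the article.

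**The concern.** BMI is weight in kilograms divided by height in metres squared. All three printed formulas put height on top and square the weight. Two of the three are outcome definitions, one of them for the primary outcome, so this is more than a slip in background text.

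It does not look like an effect of reading the PDF. Each unit stays with its own measurement (metres with height, kilograms with weight), the exponent is intact, and the same string occurs in three separate sections.

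What is at stake is the use made of BMI here. This feasibility study is meant to supply the variability, arm difference and ICC for the definitive trial, and *Intervention impact measures* says the measures may be carried into that trial. A derivation coded literally from the text would corrupt those inputs. Conversely, code that computes BMI correctly would disagree with the document it is checked against.

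**Working it through.** The protocol states no BMI value, so there is no figure to reproduce. The check evaluates the printed and the standard formula side by side. All body sizes below are assumptions chosen for illustration; none comes from the protocol.

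**Formulas.** With w = weight in kg and h = height in m:

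- standard BMI: B = w / h², in kg/m²
- as printed: P = h / w², in m/kg²

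**Values.**

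| Assumed person | B = w/h² | P = h/w² |
|---|---|---|
| Child, 12 kg, 0.87 m | 12/0.7569 = 15.9 | 0.87/144 = 0.0060 |
| Child, 14 kg, 0.95 m | 14/0.9025 = 15.5 | 0.95/196 = 0.0048 |
| Child, 16 kg, 1.00 m | 16/1 = 16.0 | 1/256 = 0.0039 |
| Child, 20 kg, 1.00 m | 20/1 = 20.0 | 1/400 = 0.0025 |
| Adult, 70 kg, 1.65 m | 70/2.7225 = 25.7 | 1.65/4900 = 0.00034 |

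**Direction at fixed height.** For the two children of 1.00 m, raising weight from 16 to 20 kg raises B from 16.0 to 20.0 and lowers P from 0.0039 to 0.0025.

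**P is not the reciprocal of BMI.** The reciprocal would be h²/w. Substituting w = B·h² into P gives P = h/(B²·h⁴) = 1/(B²·h³). P therefore depends on height as well as on BMI. Two children with the same BMI but heights of 0.90 m and 1.00 m would differ in P by a factor of 1/0.90³ = 1.37.

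**The ranking is not simply reversed.** The child of 12 kg and 0.87 m has a higher BMI than the child of 14 kg and 0.95 m (15.9 against 15.5), and also a higher P (0.0060 against 0.0048). In an illustrative simulation (height mean 0.95 m, SD 0.04; BMI log-normal with median 16 and log-SD 0.08, independent of height), the rank correlation of P with true BMI was about −0.77. The rank correlation of P with height was about −0.60, although true BMI was unrelated to height by construction. Changing the sign of P afterwards would not recover BMI.

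**What depends on it.** The 120 parents, the 12 centres and the three progression criteria (local authorities, centres, parents) involve no BMI value. The quantities that do depend on BMI are planned results: its variability, the arm difference and the ICC.

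**The case against.** The strongest reply is that the outcome is correctly named. A BMI z-score and BMI are standard measures, the formula is only a gloss in parentheses, and the sections that govern the analysis refer to BMI with no formula. Nothing in the article shows that anyone would compute from the parenthesis. If someone did, values near 0.006 instead of near 16 could not be placed on a BMI reference, and the error would surface at the first derivation. Height and weight are collected as such, so nothing would be lost. No progression decision rests on BMI, and "the analysis will focus on descriptive statistics and confidence interval (CI) estimation rather than formal hypothesis testing".

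Most of this stands, and it limits the seriousness of the point. It does not make the printed definition right. The article offers no correct formula to fall back on, and the obviousness of an error is a poor reason to leave it in a primary outcome definition.

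A reader might go further and infer that the trial's primary outcome is something other than BMI, or that its results will come out reversed. The article supports neither. The first lets a faulty gloss override a named standard measure. The second assumes literal use, which the article does not show, and a strict reversal holds only at fixed height.

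**Conclusion.** The printed BMI formula is wrong in all three places where one is given, and it should be corrected. The outcomes themselves are rightly named, so this is a definitional drafting error, best counted once.

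Its consequence is conditional. If the formula were applied as written, the result would not be BMI, and the SD, arm difference and ICC intended for the definitive trial's sample size would be invalid. If the derivation already uses the standard formula, only the text is at fault. No figure or progression criterion now in the protocol changes in either case.

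That the formula is inverted needs no assumption. The sizes quoted rest on assumed body measurements, and the rank correlations on an assumed distribution of height and BMI.

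**What to change.** Replace the expression with weight(kg)/height(m)² under *Primary outcome*, *Secondary outcomes* and *Abbreviations*. Confirm that the derivation programme computes BMI this way before converting the child's value to the age- and gender-adjusted z-score. The primary outcome already specifies that z-score, so its wording needs no other change on this point.

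The cost is three text corrections and one check of the programme. Design, measurements, recruitment and sample size are unaffected.

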#### Secondary outcomes

Secondary outcomes were as follows:Primary caregiver BMI (measured height(m)/weight(kg)^2^) and waist circumference (cm).Family eating/activities using the validated Golan Family Eating and Activity Habits Questionnaire (21 items) [24] assessing activities such as leisure time activities, eating habits and style, hunger and satiety cues, exposure to and availability of problematic foods and stimulus control, and frequency of parent and child eating meals and snacks together.Parenting self-efficacy, gathered via the Dumka Parenting Self Agency Measure (5 items) [25]. This questionnaire measures parents’ overall confidence in their ability to act successfully in their parental role.Feeding, collected via the Baughcum pre-schooler feeding questionnaire (37 items) [26]), used to measure maternal feeding practices, child eating behaviours and maternal beliefs.Dental health via a bespoke questionnaire based on the Dental Health Survey of Children and Young People by the University of Leeds, School of Dentistry, to measure the potential wider impact of HENRY and a child’s dental health (Dental Questionnaire). This contains 6 questions related to tooth brushing and dental attendance and whether the child has received general anaesthetic treatment.

### Process evaluation

As this study is aimed at determining the feasibility of undertaking a definitive trial to evaluate the clinical effectiveness of the HENRY programme, the focus of the process evaluation will be to measure contamination, acceptability and implementation. The process evaluation will follow guidance from the Medical Research Council (2015) and measure relevant constructs proposed by Baranowski and Stables [27]. This evaluation will also facilitate accurate reporting requirements of the TiDieR checklist [28]. The objectives of the process evaluation are the following:To explore the extent of contamination between intervention and control arms by monitoring staff and facilitator overlap between centres via staff movement questionnaire and holding interviews with managers, facilitators and staff to assess how adoption (or previous adoption) of the HENRY approach influences individual and centre-level practice.To explore contamination and associated impact on outcomes between parents through social networks by holding focus groups with parents from intervention and control arms.To determine the extent to which all programme sessions are delivered as planned, including dose and content delivered, quality, schedule and duration via ongoing report from HENRY central office who routinely measure the implementation and quality assurance of programmes.To investigate barriers to maintaining delivery of the programmes over the trial period at the local authority and children’s centre level via interviews with managers and local authority commissioners.To determine the acceptability of recruitment processes and data collection methods by holding interviews with commissioners, managers, staff and parent focus groups). NatCen fieldworkers will also provide feedback on the acceptability of baseline and follow-up visits via formal debriefing sessions.

Qualitative data collection will occur at multiple time points throughout the study. Local authority commissioner interviews will be held approximately 3–6 months from randomisation of children’s centres (to allow time for centre set-up) to discuss their views on barriers and levers to taking part in the research. Manager interviews will take place 12 months after centres opening to recruitment to enable them to draw on their experience of the study as a whole to discuss barriers to implementation and potential sources and impact of contamination. Interviews with children’s centre staff and HENRY facilitators, and focus groups with parents will be held periodically throughout the study, coinciding with the end of each HENRY programme, where acceptability and contamination will be explored.

All interviews and focus groups will be transcribed by members of the research team and imported in to NVivo data analysis software [29] to assist with coding and management. Qualitative data analysis will be guided by a deductive organising framework devised from the process evaluation research objectives (contamination, implementation and acceptability) and interview and focus group topic guides. Inductive thematic analysis will then be applied to identify codes and sub-codes, and potential relationships between these codes [30]. The primary coding of qualitative data will be undertaken by WB followed by second coding from another team member. Ongoing analysis will discussed with the wider research team and consensus reached for the content of themes and their influence on the subsequent design of a definitive trial.

### Health economics

The Health Economics component of a future definitive trial will aim to assess the within-trial cost-effectiveness of HENRY to reduce preschool obesity. For the feasibility study, a full cost-effectiveness analysis will not be conducted, but we will check the completeness and the ability to obtain quality of life (EQ-5D) [31] and health care resource use data for the child’s health and the parent within the NHS (health services, hospital, social services) as well as time off work in relation with HENRY. The feasibility study will therefore be an opportunity to identify the most appropriate way to collect the data needed to assess the cost-effectiveness in a definitive trial.

A study-specific health resource use questionnaire will be used to collect information on primary and secondary health care utilisation for both the parents and the child at follow-up. We will collect out of pocket expenses such as parents’ expenses in relation with travel for the intervention and other private expenses (e.g. extra food expenses, extra activities) to improve child’s diet. We will also collect parents’ lost productivity (time off work) in relation to child’s health and attendance to the programme.

Wherever possible, unit costs for resources will be obtained from national sources such as the British National Formulary [32] and the PSSRU Costs of Health and Social Care [33]. NHS and social service resource use will be identified through direct observation of the treatment provided within the feasibility study and through the structured questionnaire for collection of all other service use.

### Statistical analysis

Recommendations for feasibility studies suggest that at least 30 participants per group will allow sufficient precision when estimating study summary measures [34]. We plan to recruit two local authorities and 120 parents to give confidence that a phase III multi-centre trial can be successfully conducted [34, 35].

As this is a feasibility study, the analysis will focus on descriptive statistics and confidence interval (CI) estimation rather than formal hypothesis testing (i.e. no formal evaluation of the study interventions will be conducted as part of this feasibility study). The trial is not powered to provide a precise estimate of the level of clustering relating to group effects, but it will allow an investigation of this effect, which will inform the sample size estimation for the definitive trial. No formal analyses are planned until after the trial is closed to recruitment and follow-up and the required number of local authorities/centres have been randomised and the required number of parents have been registered. Final analysis will be carried out when all available outcome data has been collected.

The feasibility and success of the recruitment strategy will be evaluated by summarising the screening, eligibility, consent and randomisation/registration processes, including the numbers of local authorities/centres/parents involved during each stage. Reasons for non-participation in the study will be summarised. The total number of parents registered will be summarised, overall, by month/programme (as appropriate) by centre and local authority. The length of time taken to train and certify staff to deliver the HENRY programme will be detailed by HENRY staff. The number of staff attending training/certified will be summarised overall and by centre. Facilitator response to training will be captured as part of the process evaluation.

Participant retention during follow-up, including the number of centres/parents withdrawing from the study and the timing of and reasons for the withdrawal will be presented overall, by arm and time-point. We will also report losses to follow-up over time. We will also report the difference and its confidence intervals (CI) for follow-up rates between the intervention and control groups (to identify large differences between the arms). Levels of missing self-reported outcome data, both at the individual item level and for entire outcome measures will be reported overall, by time-point and by treatment arm.

Centre environment, family eating/activities, parenting self-agency, pre-schooler feeding and dental health at baseline and at 12 months post registration will be summarised overall, by arm and by time-point and where appropriate by centre (centre environment). 95% CI will be constructed for the differences in these outcomes between control and intervention groups. Mean activity per day will be summarised overall, by arm and by time-point.

In order to inform the sample size calculation for the definitive trial, we will calculate the gender-adjusted BMI, overall and per arm together with corresponding 95% CI. We will also compare the variability of gender-adjusted BMI between arms. As variation surrounding the intra-class correlation coefficient (ICC) estimate is likely to be large, we will estimate the ICC after controlling for covariates and constructing a CI [34, 36] to obtain a range of plausible estimates from which a variety of sample sizes can be calculated. A conservative approach would be to use the 80% upper one-sided confidence limit of the ICC estimate [34] in the sample size calculations.

To assess compliance with and fidelity of delivery of HENRY, the timing of delivery of the first HENRY programme will be summarised overall and by centre. Reasons for delivery post 4 weeks after receiving training will be presented by centre. In addition, the number of HENRY programmes delivered per centre, attendance rates and reasons for absence will be presented.

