### Design

This is a multi-centre, open labelled, two group, prospective, cluster randomised, controlled, feasibility study aiming to recruit 120 parents from 12 children’s centres (Fig. 1).

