### Unit of randomisation

Following relevant approvals, up to six centres (minimum 4) within each local authority will be randomised to the intervention or control in a 1:1 allocation ratio (HENRY; control) by the Leeds Clinical Trials Research Unit (CTRU) statistician (MC). Minimisation, will be used to ensure the treatment groups are well balanced for size of children’s centre (numbers of permanent centre members of staff not including staff using the centre such as health visitors and nursery workers) (≤eight/>eight members of staff); area level ethnicity (< 80%/≥ 80% White British (Census data)); and area level deprivation (≤ 10%/> 10% ranking within Index of Multiple Deprivation at the Lower Layer Super Output Area).

After randomisation, the CTRU will notify HENRY central office, the local authority lead and the children’s centres of the outcome in order to instigate necessary training arrangements. Notification will be via a secure file transfer system. NatCen will not be notified to maintain blinding of the central NatCen researchers as well as the NatCen interviewers performing the recruitment and data collection.

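### The planned 95% CIs for between-arm differences in the behavioural outcomes name no baseline adjustment, although baseline scores are held and the arms recruit parents by different routes

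*Protocol article*

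**What the plan says.** The Statistical analysis section sets out the outcomes and the contrast in two consecutive sentences. First, "Centre environment, family eating/activities, parenting self-agency, pre-schooler feeding and dental health at baseline and at 12 months post registration will be summarised overall", and also by arm and time-point. Then, "95% CI will be constructed for the differences in these outcomes between control and intervention groups". No model, covariate or baseline term is named for these differences. The next paragraph of the same section does name adjustment, but for another quantity: "we will estimate the ICC after controlling for covariates".

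On baseline collection, the section Intervention impact measures says: "Data from the following measures will be collected at the baseline and follow-up to support the feasibility objectives".

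On how parents enter the arms, the Design section limits registration in HENRY centres to parents enrolled on a HENRY programme. Recruitment and consent (Parents) takes control parents from other activities at the centre, with Stay and Play as the example. Both steps come after centres are randomised. The minimisation factors under Unit of randomisation are centre size, area ethnicity and area deprivation; none is a parent characteristic.

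**The concern.** The contrast and the confidence level are stated, and covariate control is named for one estimate in the section but not for this one. The natural reading is therefore a raw difference between arms at follow-up.

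In this design a baseline gap need not be a chance matter. Parents who sign up for a healthy-lifestyle course may differ at entry from parents at general sessions, and in the very things measured: feeding, family habits and parenting confidence. A raw 12-month difference mixes that starting gap with any change, and it leaves unused the covariate most likely to predict the 12-month score.

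These measures are candidates for the definitive trial. The Feasibility outcomes section also plans to set sources of contamination against outcome data, without saying which outcomes. An interval centred partly on an entry gap would be a poor input to either use.

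**Working it through.** **Inputs from the article.** The Design section gives the target: "aiming to recruit 120 parents from 12 children’s centres". With 1:1 allocation of centres this is 6 centres and 60 parents per arm, and 120/12 = 10 parents per centre. That exceeds the 30 per group cited under Statistical analysis. The article states no interval width, SD, correlation or ICC for these outcomes, so there is no figure of its own to reproduce.

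**Assumed inputs.** Baseline to 12-month correlation r = 0.3, 0.5 and 0.7; ICC = 0.01, 0.05 and 0.10; equal SD at both time-points; all 60 per arm followed. Results are in SD units.

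**1. Precision, same handling of clustering (none here).** Raw half-width = 1.96 × sqrt(2/60) = 0.358. The adjusted half-width is this × sqrt(1-r²).

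| r | sqrt(1-r²) | Adjusted half-width | Narrower by |
|---|---|---|---|
| 0.3 | 0.954 | 0.341 | 5% |
| 0.5 | 0.866 | 0.310 | 13% |
| 0.7 | 0.714 | 0.256 | 29% |

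The ratio does not depend on n. With 48 per arm (80% follow-up, assumed) the raw half-width is 0.400, and the adjusted values are 0.382, 0.346 and 0.286.

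**2. Baseline gap.** Adjustment shifts the estimate by about r × gap. Take a gap of 0.3 SD, r = 0.6 and no programme effect.
- If the groups regress to a common mean, the raw 12-month difference is 0.6 × 0.3 = 0.18 and the adjusted difference is about 0.
- If the gap persists in full, the raw difference is 0.30 and the adjusted difference is 0.30 - 0.18 = 0.12.

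For a gap of 0.2 SD, the amount removed is 0.06, 0.10 and 0.14 at r = 0.3, 0.5 and 0.7.

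**3. Clustering.** Design effect = 1 + (10 - 1) × ICC = 1.09, 1.45 and 1.90. With t on 10 df (2.228), the raw half-width is 2.228 × sqrt(2/60 × design effect) = 0.425, 0.490 and 0.561. The individual-level 0.358 is narrower than all three. At ICC 0.05 and r = 0.5, adding the baseline score and allowing 9 df (2.262) gives 2.262 × sqrt(2/60 × 1.45) × 0.866 = 0.431, against 0.490 raw. This takes the ICC as unchanged by adjustment.

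**4. Centre environment.** The unit is the centre, so there are 12 observations and one covariate takes the df from 10 to 9. The multiplier rises by 2.262/2.228 = 1.015, which offsets part of the 5% gain at r = 0.3.

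**The case against.** The strongest reply is that the plan fixes nothing wrongly. The article does not call the differences unadjusted, and estimators for secondary outcomes are commonly left to a full protocol or analysis plan, neither of which is at hand. This stands as far as it goes. A reader might infer that the plan commits to unadjusted differences; the text does not establish that. It does state the contrast, and it names adjustment only for the ICC, so the raw reading is the natural one and worth closing off.

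The second reply is that little rests on these intervals. The Statistical analysis section calls the analysis descriptive, with no formal evaluation of the intervention. The progression rules count local authorities, centres and parents. The sample-size inputs concern BMI, the ICC and cluster size. This stands and sets the severity.

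Third, summaries by arm and time-point would show a baseline gap, and the intervals may be meant for both time-points. This also stands, but showing a gap does not correct the 12-month interval.

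Fourth, the benefit can be overstated. A reader might infer that the reported intervals will be too wide, or that adjustment would make the arms comparable. Neither follows. An interval that ignores centres could be too narrow overall, and adjustment leaves persistent or unmeasured selection in place. The recruitment argument does not apply to centre environment, which is measured on the randomised units, and the factor sqrt(1-r²) does not carry over to categorical dental items.

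**Conclusion.** The point holds as a minor improvement to the analysis, not as an error in the plan. If the differences are raw 12-month contrasts, they include any entry gap between differently recruited parents. Compared with baseline-adjusted intervals that treat clustering in the same way, they are wider by a factor of 1.05 to 1.40 for r from 0.3 to 0.7, so adjustment would narrow them by about 5% to 29%. It would also remove about r times the gap.

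These sizes rest on assumed correlations and a linear model with equal SDs, and the precision factor applies to scale scores. For centre environment the benefit is precision only. No progression decision or sample-size calculation depends on the result.

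**What to change.** Add a sentence on the estimator to the analysis wording:

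- **Parent-reported scale scores:** take each 12-month between-arm difference and its 95% CI from a model with arm and the baseline score of the same measure, allowing for centre.
- **Categorical dental items:** use a model suited to the item type.
- **Centre environment:** if baseline is included, fit the model at centre level and accept the loss of one degree of freedom among 12 centres.
- **Reporting:** keep the raw summaries by arm and time-point, and continue to describe the intervals as descriptive, because adjustment does not remove unmeasured or persistent selection.

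The cost is slightly more analysis work and a simple rule for missing baseline scores. No further data or participants are needed.
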